## Abstract

**Background:**

While many malaria-endemic countries have health management information systems that can measure and report malaria trends in a timely manner, these routine systems have limitations. Periodic community cross-sectional household surveys are used to estimate malaria prevalence and intervention coverage but lack geographic granularity and are resource intensive. Incorporating malaria testing for all women at their first antenatal care (ANC) visit (i.e., ANC1) could provide a more timely and granular source of data for monitoring trends in malaria burden and intervention coverage. This article describes a protocol designed to assess if ANC-based surveillance could be a pragmatic tool to monitor malaria.

**Methods:**

This is an observational, cross-sectional study conducted in Benin, Burkina Faso, Mozambique, Nigeria, Tanzania, and Zambia. Pregnant women attending ANC1 in selected health facilities will be tested for malaria infection by rapid diagnostic test and administered a brief questionnaire to capture key indicators of malaria control intervention coverage and care-seeking behaviour. In each location, contemporaneous cross-sectional household surveys will be leveraged to assess correlations between estimates obtained using each method, and the use of ANC data as a tool to track trends in malaria burden and intervention coverage will be validated.

**Results:**

This study will assess malaria prevalence at ANC1 aggregated at health facility and district levels, and by gravidity relative to current pregnancy (i.e., gravida 1, gravida 2, and gravida 3 +). ANC1 malaria prevalence will be presented as monthly trends. Additionally, correlation between ANC1 and household survey–derived estimates of malaria prevalence, bed net ownership and use, and care-seeking will be assessed.

**Conclusion:**

ANC1-based surveillance has the potential to provide a cost-effective, localized measure of malaria prevalence that is representative of the general population and useful for tracking monthly changes in parasite prevalence, as well as providing population-representative estimates of intervention coverage and care-seeking behavior. This study will evaluate the representativeness of these measures and collect information on operational feasibility, usefulness for programmatic decision-making, and potential for scale-up of malaria ANC1 surveillance.

**Supplementary Information:**

The online version contains supplementary material available at 10.1186/s12936-023-04521-6.

## Background

Malaria continues to be a significant cause of morbidity and mortality worldwide, and progress toward malaria control and elimination targets in many countries has now stalled due to a range of complex issues, including increased insecticide resistance, suboptimal control strategies, weak public health systems, reduced funding, and shifting global health priorities [1]. There were an estimated 247 million malaria cases in 2021, an increase from 227 million cases in 2019 [2, 3].

Health surveillance systems continuously monitor disease trends that inform the planning, implementation, and evaluation of prevention and control programs, as well as the allocation of health resources. The World Health Organization’s *Global Technical Strategy for Malaria 2016–2030* describes surveillance as a key pillar of national and subnational strategies, necessary at all levels of malaria burden to achieve elimination [4]. However, current surveillance systems are costly and/or prone to error. Malaria-endemic countries have implemented standardized, electronic-based health management information systems (HMISs) on platforms such as the District Health Information Software 2 (DHIS2), which can provide real-time, monthly health facility data to measure trends in clinical malaria from outpatient department visits. However, timeliness and quality can be limited by the fact that the data are often collected on paper registers and must be tallied and uploaded to the DHIS2 system. Another key limitation is that these data are collected from public health systems and are subject to patient care-seeking behavior, and thus may not be representative of malaria transmission in the broader community [5]. Further, calculating accurate incidence measurements at the most granular level requires accompanying information about the population at the level of the health facility catchment area. In addition, although other country data platforms may exist, HMISs themselves do not currently collect information on intervention coverage or use and, despite recent improvements, data quality remains a limitation of these systems in many contexts [2]. In combination, these limitations mean that in the *World Malaria Report 2021*, the World Health Organization (WHO) deemed that the quality of surveillance data did not permit a robust estimate of disease burden from the number of reported cases for 30 malaria-endemic countries, all of which were in Africa [2]. Moreover, there are currently no routine indicators with which to assess trends in exposure to malaria in pregnancy, a key driver of many adverse pregnancy and birth outcomes, and a substantial contributor to overall malaria burden [6, 7], nor is there an indicator to assess the prevalence of asymptomatic malaria infections that contribute significantly to transmission.

Household cross-sectional surveys such as demographic health surveys and malaria indicator surveys are used to measure infection prevalence among both asymptomatic and symptomatic persons combined (and specifically, among children under 5 years of age in most surveys), coverage of malaria control interventions, and care-seeking behaviours in the general population to help provide accurate estimates of these indicators. They are also the basis for many geostatistical models of malaria burden, particularly in countries lacking sufficiently robust routine data, and often serve as a cornerstone of subnational stratification and tailoring exercises, which inform strategic plan and funding application development [8]. However, household surveys are rarely powered sufficiently to detect sub-provincial differences in these outcomes and are typically implemented every 2 to 5 years, making clear longitudinal trends difficult to assess. Additionally, in comparison to routine HMIS data, cross-sectional surveys are less granular, are unable to monitor short-term changes in malaria burden, and have limited use for real-time decision-making or subnational stratification.

Integrating malaria surveillance into routine antenatal care (ANC) visits has been proposed as a strategy to obtain representative data able to monitor population trends in malaria burden and intervention coverage in real time [9]. Continuous sentinel surveillance of pregnant women by testing them at their first scheduled antenatal care visit (ANC1) before they have received intermittent preventive treatment (IPTp) could be used to measure symptomatic and asymptomatic infections, provide data on spatial and temporal trends, add robustness to subnational geostatistical models, identify geographical areas with higher-than-average transmission intensity (“hot spots”), evaluate sustained changes in transmission following new interventions, and provide an early warning of increasing transmission. Women at ANC clinics could also participate in surveys about coverage, access, and use of malaria preventive tools, potentially allowing rapid assessments of intervention coverage, use, and progress in programme implementation, all with a higher degree of granularity and temporal resolution than household surveys.

Studies indicate that pregnant women attending ANC1 would be highly representative of the overall population of pregnant women where ANC attendance is high, and potentially representative of malaria prevalence in the broader population [9–12]. ANC coverage is high in sub-Saharan Africa, with an average of 72% of pregnant women attending at least one ANC visit in countries with moderate-to-high malaria transmission [3]. Monthly ANC attendance remains consistent over time, with less seasonal variation in attendance as compared to febrile visits to the outpatient department. Additionally, there is less correlation between the reason for attendance (ANC) and the outcome of interest (malaria) as compared to outpatient department attendance, where a large proportion of people present for evaluation of fever. Prevalence estimates using ANC1-based surveillance of all women regardless of symptoms would not be affected by rates of non-malarial febrile illness [13], which are likely to influence malaria test positivity rates obtained only from individuals with fever [14].

It has also been demonstrated that malaria prevalence among pregnant women correlates with the prevalence among children under 5 years of age and other populations [10–12, 15]. A systematic review and meta-analysis comparing prevalence of malaria infection in pregnant women to prevalence in children under five in the same region and during the same period showed a strong correlation between groups, with the strongest correlation between children under five and primigravid women [9]. In Tanzania, several studies have demonstrated a correlation between malaria prevalence in pregnant women attending ANC visits and other sources of prevalence estimates. In one study, data from 8 million pregnant women attending routine nationwide malaria screening at ANC1 before their first dose of IPTp were compared to data from 15,000 children under five, the latter being the total data from population-based household surveys in Tanzania in the equivalent time period. A strong positive correlation was found between the two indicators, with ANC data able to identify temporal and district-level trends well beyond the power of the survey data [12]. This suggests that ANC-based surveillance could be a highly cost-effective way to interpolate between survey data in both time and space toward the resolution needed for timely and tailored strategic action and allocation of resources [15].

While women attending ANC1 could be a pragmatic sentinel population for deriving granular and timely information on malaria burden, this measurement platform has not been thoroughly evaluated in multiple countries against current gold standard cross-sectional household surveys. This study leverages ongoing cross-sectional household surveys and contemporaneous ANC1 data collection to assess correlations and validate the use of ANC1 data to track monthly trends in malaria burden and intervention coverage, such as coverage and use of insecticide-treated nets and care seeking for febrile illness. In addition, where population denominator data are available, a secondary analysis will be conducted to look at the relationship between ANC1 malaria prevalence and malaria case incidence data derived from DHIS2.

This protocol provides a methodology and questionnaire for other national malaria control programs that may be interested in utilizing ANC1 surveillance to understand the pros and cons of using these data.

## Objectives

The overall study objective is to assess the correlation between monthly malaria prevalence estimates obtained from ANC1-based surveillance and from cross-sectional household surveys assessing malaria prevalence among children under 5 years of age to validate the ANC1 surveillance approach as (a) representative of the metric of malaria prevalence reported by common household surveys and (b) useful for monitoring general trends in malaria burden and coverage of malaria control interventions over time.

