## Study outcomes

### Primary outcome

Monthly prevalence of rapid diagnostic test (RDT)-confirmed malaria infections among women at ANC1 (asymptomatic and symptomatic).Correlation at health facility and district level between malaria prevalence at the ANC1 (monthly or quarterly) and among children tested during cross-sectional household surveys.

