### Study settings and location

This study is leveraging several planned intervention studies, including cross-sectional household surveys (modified malaria indicator surveys) at the district or village level that collect parasite prevalence data among children under 5 years (and other age groups as well, depending on country-specific epidemiology and national malaria control programme priorities). In Burkina Faso, Mozambique, and Nigeria, study activities are aligned with surveys from the New Nets Project, an observational quasi-experimental study that is evaluating the cost-effectiveness of various types of insecticide-treated nets [16]. During the New Nets Project, annual cross-sectional surveys are conducted from 2019 to 2022, including assessments of malaria prevalence, and corresponding ANC1-based surveillance occurs in a subset of health facilities in corresponding districts. Additionally, studies assessing the impact of group ANC are planned in the catchment areas of 40 health facilities each in Geita Region, Tanzania, and Atlantique Department, Benin, with corresponding cross-sectional surveys occurring as the primary method of evaluating the impact of the group ANC intervention. Due to the COVID-19 pandemic, the group intervention was stopped early in Tanzania, but the ANC1-based surveillance assessment and cross-sectional surveys continue. Cross-sectional surveys are conducted at study baseline and endline (November 2019 and June 2021 in Tanzania, February/March 2021 and September/October 2022 in Benin). In Chadiza, Zambia, this ANC1-based surveillance pilot leverages a study assessing the impact of proactive community case management in 21 health facility catchments, with surveys conducted in May 2021 and May 2023.

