To compare ANC1 malaria prevalence to prevalence from cross-sectional surveys within the same district, ANC1 malaria prevalence are obtained for the three months surrounding the community cross-sectional surveys (i.e., the month before the cross-sectional survey, the month of the survey, and the month directly following the cross-sectional survey). The relationship between malaria prevalence at ANC1 and in the community will be quantified using mixed-effects logistic regression, accounting for likely modifiers such as age, gravidity, transmission intensity, and transmission season, and adjusting for sampling effort in time and space. To quantify the incremental value of the ANC1 data, the ability of the ANC1 data to predict population prevalence using these models will be tested using leave-one-out cross-validation for each district and compared to alternative predictive models in the absence of any ANC1 data (e.g., extrapolating district-level trends from other districts sampled within the region). With support of national malaria control programmes and operational partners, district-level data on the temporal distribution of interventions within each region will be leveraged to assess the utility of ANC1 data to capture plausible trends in intervention impact. Similar analyses will be conducted to quantify the relationship between the cross-sectional surveys, the ANC1 data, reported case incidence, and the malaria test-positivity rate (obtained by dividing the number of positive malaria tests by the number of tests performed). In addition, the use of more heuristic measures such as the Kendall correlation coefficient, which provides a summary of the extent to which prevalence ranking of each district remains constant over time [12], will be used to assess the extent to which the choice of malaria metric influences operational decision-making.

Estimates of care-seeking behaviors and indicators for bed net ownership, use, and access will be determined for ANC1 data and compared to the corresponding indicators from the cross-sectional surveys. Net use and ownership (proportion of households that own at least one bed net and proportion of households with one net for every two people) will be aggregated monthly for each sampling unit/district and correlated with monthly ANC1 malaria prevalence to compare trends.

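### The household surveys can test agreement between places and between survey rounds, but they cannot validate monthly trend tracking, and the primary correlation does not by itself isolate change over time

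*Protocol article*

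**What the plan says.** The Background of the protocol article states that the study will "validate the use of ANC1 data to track monthly trends in malaria burden and intervention coverage", with the household surveys as the gold standard. The Objectives section sets out to "assess the correlation between monthly malaria prevalence estimates obtained from ANC1-based surveillance and from cross-sectional household surveys" and makes this correlation the means of validating ANC1 surveillance on two counts. The second, part (b), is that it is "useful for monitoring general trends in malaria burden and coverage of malaria control interventions over time". The second primary outcome is "Correlation at health facility and district level between malaria prevalence at the ANC1 (monthly or quarterly) and among children tested during cross-sectional household surveys".

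The survey schedule is under Study settings and location. The New Nets Project countries (Burkina Faso, Mozambique, Nigeria) have annual rounds from 2019 to 2022. The group antenatal care studies have two rounds each: "November 2019 and June 2021 in Tanzania, February/March 2021 and September/October 2022 in Benin". Zambia also has two, "with surveys conducted in May 2021 and May 2023". Under Data analysis and modelling, "ANC1 malaria prevalence are obtained for the three months surrounding the community cross-sectional surveys".

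The same section plans a mixed-effects logistic regression with modifiers that include transmission intensity and season. It also plans leave-one-out cross-validation by district against models without ANC1 data, a look at intervention timing, similar analyses with reported incidence and test positivity, and a Kendall coefficient on the constancy of district ranking.

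**The concern.** A claim about monthly tracking needs a reference that is observed monthly, or at least often enough within a year to show rises and falls. These surveys are not. The Background itself says that cross-sectional surveys cannot follow short-term changes in burden and that their usual spacing makes trends over time hard to read.

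The statistic raises a separate problem. A correlation across facilities or districts, with countries of differing transmission combined, is high whenever high-burden places look high-burden on both measures. That bears on part (a) of the objective. It says little about part (b), which asks whether ANC1 prevalence rises and falls in a given place when community prevalence does. A programme could read a high coefficient as support for acting on monthly ANC1 movements when the evidence concerns differences in level.

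**Working it through.** **The plan's own figure.** The Sample size section asks for at least 20 facilities (correlation 0.6, two-sided alpha 0.05, 80% power). By the Fisher z method, n = ((1.960 + 0.842)/atanh(0.6))² + 3 = (2.802/0.693)² + 3 = 19.3, rounded up to 20. The figure reproduces. It counts places, not time points or changes.

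**Reference data on change over time** (Table 1; Study settings and location).
- New Nets Project: 3 + 3 + 4 = 10 districts or local government areas, with at most 4 rounds each. That is at most 40 place-rounds and 10 × 3 = 30 changes.
- Benin, Tanzania, Zambia: 2 rounds, so 1 change per place.
- With one survey a year and a three-month window, 12 − 3 = 9 months of each year have no survey comparison.
- Zambia's two May rounds give no seasonal contrast. In Tanzania and Benin the two rounds fall in different calendar months, so season and year are confounded.

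**How far place differences alone can carry the correlation.** Let w be the share of variance that lies between places (taken as equal in both sources), ρB the between-place correlation and ρW the within-place correlation over time. If place-rounds are correlated together,

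r = w·ρB + (1 − w)·ρW.

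With no tracking of change, ρW = 0 and r = w·ρB. The planned 0.6 is then reached at w = 0.6/ρB:
- ρB = 0.8: w = 0.75
- ρB = 0.9: w = 0.67
- ρB = 1.0: w = 0.60

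The documents give neither w nor ρB, so these are illustrations.

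**Simulation with sampling noise.** All variance inputs are assumed: prevalence near 30%, between-place SD 0.9 on the logit scale, ρB = 0.9, ρW = 0, within-place SD 0.3, 0.45 or 0.6. Each window has 3 × 88 = 264 women.
- 10 districts × 4 rounds, 190 children per survey: mean overall r 0.75, 0.66, 0.55, nominally significant in 99%, 97% and 91% of runs. With 420 children the means are 0.75, 0.66, 0.56.
- 21 facilities × 2 rounds, 104 children per facility (2,178/21): mean overall r 0.76, 0.67, 0.58.
- Mean within-place r is about 0 throughout.

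**Can change be measured at facility level?** In the net-study countries, Table 1 gives 190/7 ≈ 27 to 420/7 = 60 survey respondents per facility and round. At an assumed 30% prevalence, the sampling SE of a two-round difference is √(2 × 0.3 × 0.7/27) = 12 points to √(2 × 0.3 × 0.7/60) = 8 points, before clustering. At district level the same formula gives 4.7 points with 190 and 3.2 points with 420. Raw facility-level change correlations would therefore be pulled towards zero even if ANC1 tracked well.

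**The case against.** The strongest reply is that the correlation is only one part of the plan. Transmission intensity as a modifier could absorb stable place differences, depending on how the mixed model is specified. Leave-one-out validation compares against models that extrapolate trends from other districts. Intervention timing is to be used to see whether ANC1 shows plausible impact. DHIS2 supplies monthly facility data. A full analysis plan, not shown, may also say how repeated rounds enter the model.

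Much of this stands. A reader might infer that the plan puts every place-by-round point into one correlation, or that trends over time go untested. The documents support neither. They say that countries are combined and count facilities, but not how rounds are handled, and several of the planned analyses may inform trends. A reader might also infer that part (b) promises monthly trends. It speaks of general trends, and in the objective the word monthly may describe only the ANC1 estimates. The explicit monthly claim is in the Background.

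The reply does not close the gap. Leave-one-out prediction can succeed on level differences alone. Constant ranking is not agreement of changes. The DHIS2 incidence comparison is secondary, needs population denominators, and uses routine data that the Background calls dependent on care-seeking. None of these analyses is stated to isolate within-place change against the surveys. No analysis plan can make annual or two-round surveys a monthly reference.

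**Conclusion.** The concern holds in a limited form. The mismatch between the monthly claim and the survey schedule is firm, because it follows from the article's own text. The surveys support a comparison between places and a thinly informed comparison between rounds: at most 3 changes per place in 10 districts and 1 elsewhere.

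The second part is that the primary correlation does not by itself separate place differences from change. Its size is illustrative: 0.6 can be reached without any tracking once about 60% to 75% of the variance lies between places, for ρB from 1.0 down to 0.8. This assumes equal variance shares in both sources and place-rounds taken together. It does not predict what the study will find.

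The two May surveys in Zambia limit seasonal inference but hold season constant for the 2021 to 2023 change, so they are not a defect for that comparison. The point should be corrected; it does not undermine the between-place validation.

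**What to change.** 1. In the Background and Objectives, limit the trend claim to change between survey rounds, using the three-month ANC1 window. Describe any monthly comparison with DHIS2 incidence or test positivity as supportive only.
2. In the planned mixed model, split ANC1 log-odds into the place mean and each round's deviation from that mean. Report the within-place coefficient separately from the between-place association, and rest trend claims mainly on the within-place result.
3. Estimate within-place change at district level where possible, or model binomial sampling error in both sources, so that attenuation is not read as failure to track.

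The cost is a change of wording and one re-parametrised covariate, with no new data and the same model family. The drawback is that the within-place estimate is less precise than an overall correlation and rests on few rounds per place. A wide interval should be reported as inconclusive, not as evidence against ANC1 surveillance.
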